**Methods & Analysis:**

PiCTuRE is a multistage, mixed-methods, exploratory sequential investigation aimed at understanding the lived experiences of individuals donating tissue for research. It consists of three phases: Phase 1 involves an online survey to collect lived experience data, followed by semi-structured interviews to further explore individual perspectives. Thematic analysis will be performed to identify key themes. In Phase 2, patient-reported experience data will be gathered through co-design and statistically analysed to validate content for the development of the digital platform. Phase 3 will refine this intervention through iterative cycles of Phases 1 and 2, in collaboration with patients with lived experience of brain or spine tumours, to prepare it for integration into routine clinical practice.

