### Phase 3: test

Phase 3 of the PiCTuRE study will evaluate the newly co-designed, interactive, personalised digital consent platform, aiming to promote patient autonomy, shared decision-making, and personalised consent. Outcomes will be measured through both qualitative and quantitative methods, with a focus on user experience. Post-intervention, a survey and semi-structured interviews will be conducted to assess participant feedback and explore their lived experiences, including their views on discussing tissue donation for research with healthcare professionals. This phase will provide insights into the effectiveness of the intervention, with Patient Reported Experience Measures (PREMs) used to gather data on satisfaction and engagement [39, 40]. The qualitative data will help validate the quantitative findings and assess the overall success of the intervention [41]. Additionally, user feedback from post-intervention interviews will be analysed for statistical significance, contributing to the refinement of the intervention, and providing evidence for a potential new standard of care in cancer patient consent processes.

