## Participant sampling and selection

The PiCTuRE study will be promoted across various digital platforms, including social media, charity websites, and patient support sites, using posters and e-flyers. Given the rarity of the target population, a multistage purposeful random sampling method [42] will be employed to encourage enrolment and identify individuals interested in participating in online semi-structured interviews, collaborating on the co-design of the digital platform, and providing feedback during the testing phase. Recognising the lack of inclusivity in research involving diverse populations, recruitment may also be supplemented through snowball sampling [43] via social media networks and outreach to ethnic community groups. Participants will receive the study information upon clicking the link provided in the online advertisements. An overview of the inclusion and exclusion criteria for all three phases of the study is outlined in Table 1.

**Table 1 Tab1:** Overview of inclusion and exclusion criteria for phases 1 to 3

Inclusion Criteria	Exclusion Criteria
Proficiency in speaking and understanding English	Inability to communicate effectively in English
Aged 18 years or older	Under the age of 18 years old
Lived experience of having a primary tumour of the brain or spine	Unable to provide informed consent
Capable of providing informed consent	No access to internet-enabled devices (e.g., smartphone, tablet, computer)
Able to communicate via digital media	Unable to communicate using digital media
Access to an internet-enabled device (e.g., smartphone, tablet, computer)	

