## Sample size

The small sample size in this study reflects the rarity of the patient cohort, influenced by factors such as the low prevalence of the tumour type, delays in presentation and diagnosis, and post-treatment survival rates.

Recruitment and sample size will be guided by the principle of data saturation [44]. Hennink and Kaiser [45] suggest that qualitative data saturation is achieved with 9–17 participants for semi-structured interviews and 4–8 participants for focus groups.

**Phase 1a: Online Survey**– Up to 45 participants.**Phase 1b: Semi-structured Online Interviews**– Up to 10 participants.**Phase 2: Co-design Users**– Up to 6 participants.**Phase 3: Test Users**– Up to 6 participants.

To determine the sample size for Phase 1a, a calculation [46] was conducted using a 95% confidence level, a 5% margin of error, and an estimated population proportion of 3% within a population of 67 million. Based on these parameters, a sample size of 45 participants was deemed sufficient.

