### Phase 1b

Audio recordings from online interviews will be transcribed verbatim using professional transcription services to ensure accuracy and consistency. The transcriptions will then be processed in qualitative analysis software (NVivo) for detailed examination and coding. Thematic analysis [32] will be employed as the primary methodology, relying on a thorough textual analysis of the transcribed content to generate a precise and reliable dataset for subsequent analysis.

### Phase 2

PREMs outcome data will be analysed using a Statistical Package for the Social Sciences (SPSS). Correlation analysis will identify relationships between variables using correlation coefficients. Regression models will evaluate the impact of multiple variables on specific outcomes, while an Analysis of Variance (ANOVA) will assess statistically significant differences between groups. Quantitative data will be supplemented by content analysis [2, 30] of audio collected via the online co-design group sessions.

Sequential data analysis will examine the connections between findings from Phase 1 and Phase 2. These results will be triangulated to guide and inform the implementation of Phase 3.

### Phase 3

Post-intervention user experience data collected via PREMs will be analysed using the methodology outlined in phase 2 and statistically compared to the corresponding phase 2 data. Quantitative findings will be enriched by qualitative insights obtained from post-intervention online semi-structured interviews. The integration of mixed-methods data [38, 44] will facilitate a comprehensive assessment of the effectiveness of the newly developed digital tool.

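### The Phase 3 versus Phase 2 comparison of experience scores has no no-tool comparator and at most 6 raters a side, so it cannot support an effectiveness conclusion

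*Protocol article*

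**What the plan says.** All references are to the protocol article.

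- **Data analysis, Phase 3.** Post-intervention PREMs "will be analysed using the methodology outlined in phase 2 and statistically compared to the corresponding phase 2 data". Combined with the interviews, the data "will facilitate a comprehensive assessment of the effectiveness of the newly developed digital tool".
- **Phase 3: test.** "This phase will provide insights into the effectiveness of the intervention". The same section says the results may help support a new standard of care for consent in cancer patients.
- **Sample size.** "Phase 2: Co-design Users– Up to 6 participants" and "Phase 3: Test Users– Up to 6 participants". No calculation is given for either phase.
- **Phase 2: build.** The CSQ-8 is there to measure satisfaction with the platform. CollaboRATE asks about the provider's communication on decisions. Feedback from users is fed back into the platform, so what is rated in Phase 2 is still changing.
- **Data analysis, Phase 2.** The methods carried into Phase 3 are correlation, regression and ANOVA: "an Analysis of Variance (ANOVA) will assess statistically significant differences between groups".
- **Participant sampling and selection.** One recruitment effort is meant to "identify individuals interested in participating in online semi-structured interviews, collaborating on the co-design of the digital platform, and providing feedback during the testing phase". Whether Phase 3 testers are new people or Phase 2 co-designers is not stated.

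**The concern.** An effectiveness statement needs a contrast between having the tool and not having it. The only quantitative contrast planned is between two sets of people who have both used it, at two stages of its development. If Phase 3 scores are higher, the later version may be better liked, or the raters may differ. If they are not, 6 against 6 would miss all but very large differences. Neither result says whether the platform helps patients decide about tissue donation.

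What is at stake is the study's closing claim. A significant p-value could be presented as evidence that the tool works, and a non-significant one as evidence that it makes no difference. The design supports neither reading.

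**Working it through.** **1. What is compared with what**

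| | Phase 2 | Phase 3 |
|---|---|---|
| Raters | co-design users, at most 6 | test users, at most 6 |
| Object | platform under construction | later, co-designed platform |
| Exposed to the tool? | yes | yes |
| No-tool, usual-consent or pre-tool measurement | none described | none described |

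The Phase 3 minus Phase 2 difference therefore combines tool version and rater. The effect of having the tool at all cancels out or is never measured. CollaboRATE does not rescue this: it rates communication, but still only among people who have used the tool.

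**2. The plan's own figure**

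The only calculated sample size is for the Phase 1a survey: n = z²p(1−p)/e² = 1.96² × 0.03 × 0.97 / 0.05² = 44.7, rounded up to 45. It reproduces, but has no bearing on Phase 3.

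**3. Precision of 6 against 6**

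Inputs: n = 6 per phase (Sample size, the stated maximum). Assumed, because the article gives none: two-sided alpha 0.05, independent groups, effects in SD units (d).

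- 95% CI half-width = t(0.975; 10 df) × √(2/6) = 2.228 × 0.577 = **1.29 SD**.
- Power from the noncentral t with 10 df and noncentrality d × √(6×6/12) = 1.732d:

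| d | Power |
|---|---|
| 0.5 | 12% |
| 0.8 | 24% |
| 1.0 | 35% |
| 1.5 | 65% |
| **1.80** | **80%** |

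- For scale, the number per group for 80% power is 2(1.96 + 0.842)²/d² (normal approximation): 15.7/0.25 = 62.8, so 63 at d = 0.5; 15.7/0.64 = 24.5, so 25 at d = 0.8.

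These are best cases, since 6 is a ceiling.

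**4. If the same people rate in both phases**

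For six pairs, the half-width is t(0.975; 5 df) × √(2(1−ρ)/6), where ρ is the within-person correlation (assumed). With ρ = 0.5 this is 2.571 × √(1/6) = 1.05 SD; with ρ = 0.3 it is 1.24 SD and with ρ = 0.7 it is 0.81 SD. Pairing helps, but the interval stays wide and step 1 is unchanged.

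**The case against.** The best defence is that the study is openly exploratory, explains its small samples by the rarity of the tumours, and states no confirmatory hypothesis for this comparison. Effectiveness is also to be judged from integrated qualitative and quantitative data, so the PREM comparison is only one strand. Both points are fair, and they limit the criticism to the quantitative strand and its wording. They do not remove it. An exploratory design justifies description, not a statistical comparison feeding an effectiveness conclusion. The interviews, also with at most 6 testers and no comparator, do not supply the missing contrast.

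A reader might infer more than the article supports:

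- **That the test will have the wrong error rate because the same people appear twice.** The shared recruitment permits overlap but does not state it, and co-design and test users are listed separately. ANOVA is named without its form, which could be repeated-measures, and such detail is commonly left to the analysis plan. Treating positively correlated pairs as independent would in any case make the test conservative: in simulation, type I error was about 1.3% at an assumed correlation of 0.5, not above 5%.
- **That co-designers' ratings bias the result upward.** The direction is not established. If authorship raises scores, it raises the Phase 2 reference and would push the difference down with new testers.
- **That the article contradicts itself on Phase 3.** The Abstract says "Phase 3 will refine this intervention through iterative cycles of Phases 1 and 2", while the Phase 3 section speaks of evaluation. But that same section says the evaluation feeds further refinement, which is ordinary iterative development.

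**Conclusion.** The point holds for the quantitative strand. As planned, the Phase 3 versus Phase 2 comparison can show at most a change in ratings between versions or raters. It cannot show effectiveness, and it is no basis for a new standard of care. This follows from the article's description of the two phases and needs no numerical assumption.

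The imprecision is a second limit: 80% power only at about 1.80 SD, 24% power at 0.8 SD, and an interval of about ±1.29 SD. Those figures assume independent groups of 6 and a two-sided alpha of 0.05.

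This should be fixed before Phase 3 is reported, but it does not undermine the development work in the earlier phases. The article does not support a stronger conclusion that the comparison is biased in a known direction or prone to false positives.

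**What to change.** 1. In the sections Phase 3: test and Data analysis, Phase 3, replace effectiveness with acceptability and usability as what Phase 3 assesses, and remove the link from these results to a new standard of care.
2. Drop the significance test of Phase 3 against Phase 2. Report PREM scores for each phase, and their difference with a 95% confidence interval, as descriptive only.
3. If anyone rates in both phases, link that person's ratings and compute the difference within person.

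This needs no extra participants or data, apart from a study identifier where people overlap. The cost is a more modest claim.

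Requiring all testers to come from outside the co-design group is not proposed. The Phase 1a survey is anonymous, and only those who leave an email address for Phase 1b can be contacted. If 6 of at most 10 interviewees join the co-design, 10 − 6 = 4 remain, fewer than the 6 testers allowed for. Such a rule could need different consent or separate recruitment.

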## Ethics and dissemination

PICTuRE has received ethical approval from the Central University Research and Ethics Department (CUREC), University of Oxford CUREC- R79248/RE001. The protocol has been written with reference to the SPIRIT (Standard Protocol Items: Recommendations for International Trials) checklist [47] and has been registered with the International Standard Randomised Controlled Trial Number (ISRCTN) registry on the 11th November 2023, with reference number: ISRCTN12601034.

## Data Availability

No datasets were generated or analysed during the current study.
